## Abstract

**Background:**

Peripheral arterial disease (PAD) affects more than 200 million of the global population. PAD represents a marker for premature cardiovascular events. Patients with PAD, even in the absence of a history of myocardial infarction or ischemic stroke, have approximately the same relative risk of death from cardiovascular causes as patients with a history of coronary or cerebrovascular disease. Despite the high prevalence of PAD and the strong association with cardiovascular morbidity and mortality, patients with PAD are less likely to receive appropriate treatment for their atherosclerotic risk factors than those who are being treated for coronary artery disease.

Atherosclerotic risk factor identification and modification play an important role in reducing the number of adverse outcomes among patients with atherosclerosis. Risk reduction therapy decreases the risk of cardiovascular mortality and morbidity in patients with PAD. In this study, we aim to evaluate the effectiveness of a lifestyle and risk factor modification intervention programme in achieving treatment goals for PAD risk factors.

**Methods:**

This is a randomised, parallel group, active-control trial to compare the effectiveness of the risk factor modification intervention programme to standard healthcare in a tertiary vascular care centre, in the reduction of modified risk factors in PAD patients. The primary outcome of this study is to evaluate the effectiveness of a lifestyle and risk factor modification intervention programme in achieving treatment goals for PAD risk factors at 3 and 12 months. The secondary outcomes are to compare the impact of the programme on clinical outcomes in PAD patients at 12 months. Secondary outcomes include amputation-free survival, clinical improvement, haemodynamic improvement, need for revascularisation procedures, outcomes of revascularisation procedures, changes in quality of life and the incidence of adverse events.

**Discussion:**

This study will provide clear evidence on the effectiveness of a lifestyle and risk factor modification intervention programme in achieving treatment goals for PAD risk factors, through a high-quality, well-powered clinical trial.

**Trial registration:**

This trial was registered (11/07/2017) on the European Clinical Trials Database (EudraCT number 2017-002964-41) and ClinicalTrials.gov (NCT03935776) which was registered on 02 May 2019.

**Supplementary Information:**

The online version contains supplementary material available at 10.1186/s13063-021-05087-x.

## Background

Peripheral arterial disease (PAD) affects more than 200 million of the global population [1]. PAD represents a marker for premature cardiovascular events [2]. Patients with PAD, even in the absence of a history of myocardial infarction or ischemic stroke, have approximately the same relative risk of death from cardiovascular causes as patients with a history of coronary or cerebrovascular disease [2]. Despite the high prevalence of PAD and the strong association with cardiovascular morbidity and mortality, patients with PAD are less likely to receive appropriate treatment for their atherosclerotic risk factors than those who are being treated for coronary artery disease [3, 4].

As PAD represents a peripheral manifestation of atherosclerosis, most traditional and novel cardiovascular risk factors are strongly associated with this condition [5–7]. Smoking, diabetes, hyperlipidaemia, hypertension, unhealthy diet and physical inactivity were identified as significant modifiable risk factors that should be targeted for secondary prevention [8–12].

Atherosclerotic risk factor identification and modification play an important role in reducing the number of adverse outcomes among patients with atherosclerosis [13]. Risk reduction therapy decreases the risk of cardiovascular mortality and morbidity in patients with PAD [13]. Because of the efficacy of these techniques, several expert committees have recommended their use in patients with PAD [8–12]. Despite clear guidelines, several studies have shown that patients with PAD are routinely undertreated for these risk factors [4], which may contribute to high rates of morbidity and mortality.

Previous studies concluded that modifiable risk factor programmes help cardiac patients achieve their risk factor modification targets, with subsequent reduction in cardiovascular events [14–16]. To our knowledge, currently, there is still no evidence to support that the implementation of a structured modifiable risk factor reduction program will lead to improved outcomes in PAD patients. However, due to the similar atherosclerotic burden in cardiac and PAD patients, we hypothesise that these risk factor modification programmes would similarly improve risk factor target achievement in PAD patients and subsequently improve their clinical outcomes and reduce their amputation rates when compared to standard healthcare.

The possibility of lifestyle and risk factor modification intervention should have a positive impact on patients’ clinical well-being and on their quality of life.

## Study objectives

### Primary objective

The primary objective of this study is to evaluate the effectiveness of a lifestyle and risk factor modification intervention programme in achieving treatment goals for PAD risk factors compared to the standard healthcare management.

### Secondary objectives

Secondary objectives are to compare the impact of the programme on clinical outcomes in PAD patients, specifically:
Amputation-free survivalClinical improvement [17]Haemodynamic improvement [17]Need for revascularisation proceduresChanges in quality of life [18]The incidence of adverse events

## Methods

### Study design

This is a randomised, parallel group, active-control trial to compare the effectiveness of the risk factor modification intervention programme to standard healthcare in a tertiary vascular care centre, in the reduction of the prevalence of modifiable risk factors in PAD patients.

This trial will randomise patients with PAD in an equal ratio to one of two treatment arms. One arm will be randomised to undergo a risk factor modification intervention programme at a community-based centre. The other arm will be provided with standard healthcare advice, in the outpatient PAD clinic in a tertiary referral vascular centre. Patients randomised into the risk factor modification intervention programme will have the intervention administered for 12 weeks. Patients will then be followed for 12 months to determine further PAD outcomes. The participant flowchart through the study is shown in Fig. 1. SPIRIT figure for this trial is given in Fig. 2.

**Fig. 1 Fig1:**
[figure not shown]
Participant flowchart through the study

**Fig. 2 Fig2:**
[figure not shown]
SPIRIT figure showing an overview of the assessment schedule at baseline and follow-up in study. ABI: ankle-brachial Index, WIfI: wound ischaemia and foot infection classification, HbA1c: glycosylated haemoglobin, BMI: body mass index, HADS: Hospital Anxiety and Depression Scale, MACE: major adverse cardiovascular event and MALE: major adverse limb event

### Study setting

Potential participants will be identified from the outpatient PAD clinic at the University Hospital Galway, Ireland (UHG). Patients will be screened and randomised at the outpatient PAD clinic in UHG.

The risk factor modification intervention programme will be administered in a nurse-led community-based centre (Croí Heart and Stroke Centre, Galway, Ireland), in the presence of a physiotherapist and dietitian. The control arm will be managed in the outpatient PAD clinic, UHG. The coordinating centre will be the Department of Vascular and Endovascular Surgery, UHG, and the School of Medicine at the National University of Ireland Galway (NUI Galway). Patients are directly supervised during the intervention. The 12-week and 1-year assessments will take place at the outpatient PAD clinic in UHG.

### Eligibility criteria

#### Inclusion criteria

Aged 18 years or moreProvide written informed consentPAD: diagnosed by at least one of the following:
Ankle-brachial index of less than 0.90 in at least one lower extremity [9]Toe brachial index of less than 0.60 [9]Evidence of arterial occlusive disease in one lower extremity detected by duplex ultrasonography, computed tomographic angiography, or magnetic resonance angiography [9]Symptomatic PAD (Rutherford category 2 and above [19])Patients should have at least one of the following risk factors:
Blood pressure > 140/80 mmHgFasting blood sugar (FBS) > 53 mmol/molGlycosylated haemoglobin (HbA1c) > 7%Total cholesterol > 5 mmol/LLow-density lipoprotein (LDL) cholesterol > 2.6 mmol/LTriglycerides > 1.7 mmol/LHigh-density lipoprotein (HDL) < 1.0 mmol/L in men and < 1.2 mmol/L in womenPhysical activity less 30 min for 5 days per weekBody mass index (BMI) > 25 kg/m^2^Waist circumference > 80 cm in women, and > 94 cm in menCurrent smoker or exposure to tobacco in any formUnhealthy diet, Mediterranean diet score less than 10 points

#### Exclusion criteria

Involvement in another clinical trial in the previous 6 monthsLegal incapacityInadequate English language ability to understand the content of the intervention programmeSignificant cognitive impairment or mental illnessRefusal to participate in a certain part of the interventionPatient suffering from a comorbidity that could affect either their physical participation in the intervention arm or influence outcomes (e.g. ischemic heart failure or severe chronic kidney disease with an estimated glomerular filtration rate of less than 30 mL/min [20])Patient is immobileContraindication to anticoagulation and antiplatelet medications or any of the risk factors treatment.

### Study screening

Patients with Symptomatic PAD (Rutherford category 2 and above [19]) will be invited to join the study. Invited patients will be provided with a pre-designed information leaflet. This leaflet will be fully explained to the patient at the initial assessment. The study researchers will answer any questions about the study. Informed consent will be obtained from the patient on a formatted consent form. Patients will be given the freedom to give consent either on the same day or at a later date in accordance with a study within a trial (SWAT), entitled “Same-day Consent vs Delayed Consent in a Randomised Trial: A Study within a Trial” [21]. This SWAT aims to ensure the rigorousness of the consent process and will run in conjunction with this randomised controlled trial.

Researchers will screen the patient for inclusion and exclusion criteria and administer a series of the following:
Record PAD risk factors such as smoking, hyperlipidaemia, diabetes, hypertension, increased body weight and the patient’s current medication.Document the Rutherford category [19], claudication distance and absolute walking distance for each patient, to assess the severity of PAD.Schedule appointments for baseline health assessments over the following month.

### Randomisation

After meeting the inclusion criteria, screened patients will be randomised to one of two treatment arms. One arm will receive the 12-week intensive risk factor modification intervention programme. The control arm will be provided with standard care in the outpatient PAD clinic. This is an intention to treat designed study, where patients are analysed as randomised. Each screened patient will be given a unique screening number.

Screened patients will be randomised in a 1:1 ratio of study intervention: control according to a randomisation scheme. The randomisation scheme will be produced using the PROC PLAN® procedure of the SAS®software package (version 9.2.2) using a simple randomisation strategy. The scheme will be concealed from all patients and study personnel until after database lock.

Patients will be allocated to intervention via an automated telephone system, which will not deliver the randomised allocation except after registering the subject screening number. Each screened patient who is recruited to the trial will be given a unique patient trial number.

The statistician will remain blinded to the treatment allocation until all the data have been analysed to minimise bias. Outcome assessors and data analysts will be blinded; however, in the event of an adverse event outcome, assessors will be unblinded.

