#### Standard healthcare

The control group will receive the standard healthcare advice provided to PAD patients in the outpatient PAD clinic. In this study, standard care will be conducted by the researchers which include:
Advising patients to quit smoking, regular exercise and healthy eating, but neither structured intervention nor organised cessation plans will be addressed.Non-specific interventions, such as providing patients with educational material on general health problems.

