#### Secondary endpoints

Secondary endpoints of PAD outcomes are based on the Society for Vascular Surgery (SVS) reporting standards [17]:
Amputation-free survival; defined as time spent free from any major above ankle amputation [17]Hemodynamic improvement: defined as an increase in the ABI by at least 0.10 [17]Clinical improvement: which is defined as an upward shift by at least one Rutherford category. However, PAD patients suffering from actual tissue loss (Rutherford category 5 [19]) should move up two Rutherford categories to be considered improved [19].Re-intervention or stenosis rate; any re-intervention or stenosis among patients who already underwent vascular surgery [17]Freedom from major adverse cardiovascular events (MACE). MACE is defined as any major cardiovascular event such as myocardial infarction, cerebrovascular accident or death [17].Major adverse limb events (MALE). MALE is defined as any major amputation or revascularization procedure [17].Revascularisation-free survival; defined as time free from any revascularisation procedure regardless of if it were an endovascular intervention or an open surgery [17].Change from baseline of the following risk factors:
a-BMI (measured in kg/m^2^)b-HbA1c (measured as a percentage)c-Total cholesterol (measured in mmol/L)Health-related quality of life [18]; assessed using the Dartmouth Cooperative Information Project (COOP) charts at enrolment and after 1 year. The COOP charts measure six core aspects of functional status: physical fitness, feelings, daily activities, social activities, change in health, pain, and overall health. The instrument consists of six charts, referring to the abovementioned aspects of functioning. Each chart consists of a simple title, a question referring to the status of the patient and an ordinal 5-point response scale illustrated with a simple drawing. Each item is rated on this 5-point ordinal scale ranging from 1 (no limitation at all) to 5 (severely limited); for “change in health” score 1 means “much better” and score 5 “much worse”. The designers do not advocate summing the responses to gain a single index figure of health status

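### Outcome assessors are unblinded without restriction after an adverse event, a category that plausibly includes several secondary endpoints; the rule also conflicts with the concealment statement

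*Protocol article*

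**What the plan says.** In the protocol article, the Randomisation section blinds those who assess outcomes and those who analyse the data, and adds an exception in the same sentence: "in the event of an adverse event outcome, assessors will be unblinded". Earlier in the same section it says: "The scheme will be concealed from all patients and study personnel until after database lock".

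Under Secondary endpoints, several efficacy outcomes are events that harm the patient:

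- MACE: "MACE is defined as any major cardiovascular event such as myocardial infarction, cerebrovascular accident or death".
- MALE: "MALE is defined as any major amputation or revascularization procedure".
- Amputation-free survival: "defined as time spent free from any major above ankle amputation".
- Revascularisation-free survival: "defined as time free from any revascularisation procedure regardless of if it were an endovascular intervention or an open surgery".

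Safety endpoints lists the incidence and severity of adverse events, together with side effects and interactions of medication started in the trial. It neither includes nor excludes the events above. One-year assessment collects MACE, MALE, amputation, revascularisation and residual stenosis at the visit that also repeats the baseline measures.

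**The concern.** Patients and those who deliver the two forms of care cannot be blind to a 12-week community programme compared with clinic advice. Keeping the assessor unaware of the arm is therefore an important safeguard for outcomes that need judgement or rest on the patient's report. The stated exception removes that safeguard in patients selected by what has happened to them, and some of those happenings are probably efficacy endpoints.

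Two things are at stake. The first is the classification of the event itself, for example whether an episode counts as a myocardial infarction or a stroke. The second is everything the same assessor records later in that patient. Neither calls for the assessor to know the arm, because the treating team already does.

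**Working it through.** The plan gives no figure on this point. Its only design figure, 208 patients, concerns the primary endpoint and does not enter. The check sets the sections side by side.

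**1. How wide is the exception?** The Randomisation sentence has one trigger, an adverse event, and one consequence, unblinding of assessors. It sets no limit by seriousness, by emergency or by role. The punctuation is awkward, and the comma may belong one word earlier, so that outcome assessors is the subject. Either way an assessor is unblinded.

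**2. Does the trigger reach the endpoints?** The article never says in words that MACE, MALE, amputation or revascularisation are handled as adverse events. The inference rests on two facts: two of these outcomes carry the word adverse in their names, and Safety endpoints exempts none of the four. Adverse events are the wider set, since medication side effects belong to it too. The supportable statement is that adverse events plausibly include these endpoints, not that they are the same thing.

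**3. Which outcomes are exposed?**

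| Outcome | Exposure if the assessor knows the arm |
|---|---|
| Myocardial infarction, stroke (in MACE) | Needs classification: exposed |
| Rutherford category, residual stenosis | Judgement or reading: exposed |
| Quality of life, smoking status | Self-report collected by staff: exposed |
| Revascularisation | Recorded procedure; the discretion lies with the treating team, which assessor blinding does not reach |
| Death, major amputation | Largely objective: little exposed |
| ABI (rise of at least 0.10), HbA1c, total cholesterol | Numeric: little exposed |

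**4. Does it reach the primary endpoint?** Only indirectly. Its four components are smoking cessation, BMI, HbA1c and total cholesterol, and none of them is an adverse event. A patient whose assessor was unblinded earlier could have smoking status recorded with the arm known. Smoking cessation alone can satisfy the endpoint, and the Discussion counts the smoking questionnaire among the subjective methods. The other three components are measured.

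**5. Is it consistent with the concealment sentence?** On a plain reading it is not. One sentence conceals the scheme from all study personnel until after database lock, and the other discloses allocation to some of them during follow-up. If scheme means only the full list, the two could stand together. The article would then contain no statement that an assessor stays blind to an individual patient's arm once that patient has had an event.

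**6. Size.** No adverse event rate is given. For scale only, and purely as an assumption, 10% to 30% of 208 patients would be 0.10 × 208 = 20.8, about 21, to 0.30 × 208 = 62.4, about 62. These are patients whose assessor would be unblinded at some point. They are not biased results, and the point does not depend on the range.

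**The case against.** The strongest reply is that the clause may mean less than it says. Adverse events stand under their own safety heading, so the exception may have been written for safety reporting only, and the full protocol may limit it. That is possible, and it is why the overlap is stated here as an inference. It does not remove the point, because the article states a rule without limits and that rule, followed as written, unblinds assessors.

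It is also fair to say that much of the trial is protected in other ways. The statistician and data analysts are blinded, the telephone system withholds the arm until the screening number is registered, and several outcomes are hard events or numbers. All of that stands and limits the severity, but blinded analysts do not protect the recording of an outcome.

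A reader might infer more in three directions that the document does not support:

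- **More unblinding in the programme arm.** Weekly contact is described only for the 12-week programme. Both arms have their 12-week and one-year assessments in the same clinic, and MACE and MALE are collected at one year. A difference between arms is possible but not shown.
- **Assessors who also give the care.** The article says that "standard care will be conducted by the researchers", but nowhere that these researchers assess outcomes.
- **Essentially all MACE and MALE classified unblinded.** This would require that every such event is handled as an adverse event and that the unblinded assessor is the one who classifies it. Neither is stated.

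**Conclusion.** The point holds in a limited form. The unblinding exception is unrestricted, plausibly reaches several secondary endpoints, and conflicts on a plain reading with the concealment sentence in the same section. This is a rule the article fixes badly, not a detail left to another document.

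The effect is mainly on secondary endpoints, and within them on classification of myocardial infarction and stroke, Rutherford category, residual stenosis and quality of life. Smoking status gives an indirect route to the primary endpoint. The size cannot be derived from the article. The conclusion rests on two assumptions: that the named endpoints count as adverse events, and that an assessor once unblinded continues to assess the same patient. It would be wrong to infer that the primary comparison is undermined or that assessor blinding is the trial's only protection. The change should be made, but it does not threaten the trial's main result.

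**What to change.** Replace the exception with wording to this effect: allocation is disclosed only to those who manage the patient's safety or report the event; outcome assessors remain blinded for all outcomes, including MACE, MALE, residual stenosis and Rutherford category; any unblinding of an assessor is logged with its date and reason and reported by arm.

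Reword the concealment sentence to agree, saying whether it refers to the randomisation list or to individual allocations, and from whom each is kept.

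Keep every patient and every event in the intention-to-treat analysis. Do not drop assessments made after unblinding. The trigger is itself an outcome, so such an exclusion would select on outcome and could remove the endpoint events themselves.

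The cost is a small division of tasks among existing staff, since blinded assessors are already planned, and an amendment that goes first to the ethics committee. Recruitment began on 1 June 2018, so the amendment would govern assessments still to come; unblinding that has already happened should be entered in the log.

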### Baseline, prior to intervention

All randomised patients will undergo a full baseline assessment prior to their intervention:
PAD assessment;
Ankle-brachial index (ABI)Digital pressureRutherford category [19]Wound ischaemia and foot infection classification (WIfI) [22]Blood samples including:
Fasting blood lipidsFasting glucoseHbA1cBlood pressure documentationAnthropometric measurements including:
BMIWaist circumferenceSub-maximal functional capacity exercise testing including:
Shuttle test [23]Claudication distance [24]Absolute walking distance [25]Behavioural and psychological survey using the Hospital Anxiety and Depression Scale (HADS) [26].Health-related quality of life assessment: Dartmouth Quality of Life score [18].Smoking status assessment using the Fagerstrom Test for Nicotine Dependence [27].Physical activity assessment: Godin and Shepard Leisure Exercise Questionnaire [28].Nutritional assessment through the Mediterranean Diet Questionnaire [29].

